#### Treatment duration

Generally, the infants will be placed under FS-PT/CPT from 9:00 am to 5:00 pm (target minimum duration of 5 hours per day for any infant in the study at 10:00 am, or 65% of total time between start time and 5:00 pm for infants enrolled after 10:00 am). The infants’ eyes will be protected with low-cost eye covers made from the elastic tops of any color socks. Bilirubin kinetics will only be calculated for infants who are able to spend at least 5 hours in FS-PT/CPT.

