### Observational study on the safety and potential efficacy of filtered sunlight phototherapy

A recent comprehensive systematic review of available evidence worldwide on PT found no randomized controlled trials (RCTs) dealing with either sunlight or environmental light
[26]. Prior to our proposed RCT to establish the effectiveness of FS-PT compared with CPT in a larger sample of infants, we conducted an observational study to evaluate safety and potential efficacy of two previously tested films for use in an inner-city maternity hospital in Lagos, Nigeria. FS-PT safety was determined through close monitoring of infant temperature, hydration status, and skin for signs of possible sunburn. Therapy was deemed safe on a given day if the infant did not have to be removed from phototherapy due to needing physician treatment for sunburn or dehydration, due to persistent temperature instability defined as two or more episodes of temperatures <35.0 or >39.0°C, or due to failure to return to normothermia (defined as 35.5 to 38.0°C) within 1 hour of being removed from FS-PT. Efficacy was evaluated by measuring the rate of rise/decline in total serum/plasma bilirubin (TSB) levels. Treatment was deemed safe and efficacious if the infant was able to stay in the FS-PT canopy for ≥5 hours per day and the rate of rise of TSB was <0.2 mg/dl/hour for infants ≤72 hours of age or if TSB decreased for infants >72 hours of age. This study was concluded in August 2012, details of which are scheduled for publication shortly. In summary, 203 term and near-term newborns (≤14 days old) with clinically significant jaundice as assessed by TSB levels were enrolled. They received treatment under a FS-PT canopy over a period of 227 days. Hourly measurements of axillary body temperatures and monitoring of sunburn, dehydration, and irradiances of FS-PT were performed. The results showed that FS-PT was efficacious in 94% (164/175) of the infants studied. Average irradiance from FS-PT was 37 ± 14 (range 8 to 65) μW/cm^2^/nm as measured by the Bili-Blanket Meter II^©^ (General Electric, Fairfield, CT, USA). No infant developed sunburn or dehydration, nor met exclusion criteria. Based on these favorable findings with our selected films (Gila Titanium and Air Blue 80 produced by CP Films Inc. Subsidiary of Eastman Chemical Co. Fieldale, VA, USA), we set out under the second phase of this project to demonstrate primarily in a RCT that FS-PT is just as efficacious as CPT in the treatment of infants with or at risk of severe NNJ.

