#### Evaluation criteria

Change in TSB level per hour of therapy defined as a binary variable. The TSB level will be measured immediately before beginning therapy on a given day and immediately after therapy is completed that day, and the change in bilirubin level in mg/dl per hour of therapy will be calculated. For infants who are less than 72 hours old in the morning, the treatment will be judged efficacious if the bilirubin level rises more slowly than 0.2 mg/dl per hour of therapy that day. For infants who are more than 72 hours old, the treatment will be judged efficacious if the bilirubin level falls. Efficacy will be evaluated only for days in which the treatment was deemed safe (that is, when the infant did not have to be removed from PT due to a need for physician treatment for sunburn or dehydration, persistent temperature instability defined as two or more episodes of temperatures <35.0 or >39.0°C, or failure to return to normothermia (defined as 35.5 to 38.0°C) within 1 hour of being removed from PT). The average efficacy of each type of PT, defined as the proportion of safe days where a given therapy was used in which the therapy was efficacious, will be compared. FS-PT will be considered at least as efficacious as CPT if the average efficacy on days where FS-PT was used is no worse than 10% less than the average efficacy on days where CPT was used.

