### Exit/discontinuation/withdrawal criteria

Subjects will exit the study (will cease to receive FS-PT or CPT) if any of the following conditions occur: 1) persistent temperature instability defined as two or more episodes of temperatures <35.0°C or >39.0°C; 2) failure to return to normothermia (defined as 35.5°C to 38.0°C) within 1 hour of being removed from PT; 3) physician treatment for dehydration or sunburn is required; 4) TSB level reaches exchange transfusion levels; 5) inter-current illness not compatible with PT or needing more care than can be provided in the FS-PT canopy or CPT ward; 6) infants requiring transfer to another hospital; 7) parent request; 8) subject death; 9) subject completes the protocol (TcB or TSB level is no longer elevated); 10) subject’s well-being, in the opinion of the Investigator, would be compromised by study continuation; 11) Institutional Review Board (IRB) recommendation; or 12) subject’s risk level indicates PT should be stopped.

Infants who have been withdrawn from the study will have a physical examination and a final TcB. Safety data will be analyzed for all days in which the subjects spend any time under either FS-PT or CPT.

Efficacy will be evaluated for all days in which the treatment was deemed safe (that is, when the infant did not have to be removed from PT due to a need for physician treatment for sunburn or dehydration, due to persistent temperature instability defined as two or more episodes of temperatures <35.0 or >39.0°C, or due to failure to return to normothermia (defined as 35.5 to 38.0°C) within 1 hour of being removed from PT).

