#### Treatment (stage 2)

FS-PT will be started in the morning after the irradiance level inside the canopy is at least 8 μW/cm^2^/nm, and will be stopped in the late afternoon when the irradiance level drops below 8 μW/cm^2^/nm or at any point during the day during a rainy/cloudy day when the irradiance stays below 8 μW/cm^2^/nm. If the irradiance persists below 8 μW/cm^2^/nm for more than 1 hour and the infant qualifies for PT per the AAP guideline, CPT will be initiated. If the irradiance again exceeds 8 μW/cm^2^/nm then the infant may again be placed in FS-PT.

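### The 5-hour minimum for calculating bilirubin change conflicts with the all-safe-days efficacy set and the intent-to-treat analysis, and can drop weather-shortened days from the sunlight arm only

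*Protocol article*

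**What the plan says.** All references are to the protocol article.

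- **Treatment duration.** The exposure target has two parts. Infants already in the study by 10:00 have a daily target of 5 hours. Later arrivals have a proportional one, given as "or 65% of total time between start time and 5:00 pm for infants enrolled after 10:00 am". The section then sets a condition for analysis, with no 65% alternative: "Bilirubin kinetics will only be calculated for infants who are able to spend at least 5 hours in FS-PT/CPT".
- **Evaluation criteria (primary outcome).** Bilirubin (TSB) is measured before and after each day's therapy, and "the change in bilirubin level in mg/dl per hour of therapy will be calculated". That change is dichotomised. The only restriction is safety: "Efficacy will be evaluated only for days in which the treatment was deemed safe".
- **Exit/discontinuation/withdrawal criteria.** The same set is described as complete: "Efficacy will be evaluated for all days in which the treatment was deemed safe".
- **Data collection and analysis.** Three analyses are planned: intent-to-treat by assigned treatment for each enrolled infant, as-treated, and per-protocol.
- **Treatment (stage 2).** FS-PT ends in the late afternoon, or "at any point during the day during a rainy/cloudy day when the irradiance stays below 8" (in μW/cm²/nm). CPT then replaces it only if the infant meets the AAP level for phototherapy. Trial entry is 3 mg/dl below the AAP high-risk level (Definition of high-risk threshold).

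**The concern.** An infant-day for which the change per hour is not calculated has no primary outcome. If the 5-hour condition governs that calculation, it is a second filter, applied after randomisation, on top of the safe-day rule. The two sections that define efficacy do not mention it, and it undercuts an intent-to-treat analysis of each enrolled infant.

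Two consequences need to be kept apart. First, infants treated to the plan's own target can be unanalysable. Second, the filter depends on how much therapy could be delivered, and one cause of short delivery, low irradiance, exists only in the FS-PT arm. In a non-inferiority trial, removing days on which the new treatment could not be delivered tends to favour that treatment if those days would have gone worse.

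**Working it through.** **1. The plan's sample size.** Inputs from Sample size: efficacy 80% in both arms, margin 10 points, one-sided alpha 0.025, power 80%. The unpooled normal approximation gives 252 days per arm, 504 in total, as stated. Then 504/0.9 = 560 and 560 × 1.1 = 616, also as stated. No separate allowance is made for days under 5 hours. Rainy days share the 10% allowance with withdrawals and missing data.

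**2. The 65% target against the 5-hour condition.** Target = 0.65 × (17:00 − start).

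| Start | Hours to 17:00 | 65% target (h) | Time that can be lost before falling under 5 h |
|---|---|---|---|
| 10:00 | 7 | 4.55 | 2 h |
| 11:00 | 6 | 3.90 | 1 h |
| 12:00 | 5 | 3.25 | none |
| 13:00 | 4 | 2.60 | 5 h cannot be reached |

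The target equals 5 h only when hours to 17:00 = 5/0.65 = 7.69, a start at about 09:18. It is therefore below 5 h for every infant it covers (those enrolled after 10:00). A start after 12:00 cannot give 5 h by 17:00. Late enrolment occurs in both randomised arms, so this part costs days and is not in itself selective.

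**3. Cost in power.** 616 × 0.9 × 0.9 = 499 evaluable days, about 249.5 per arm, gives power 79.7%. If a further 5% to 20% of days in both arms fell under 5 h (assumed), power would be 77.7% to 70.5%.

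**4. The arm-related part.** The irradiance stop applies to FS-PT only. The condition's wording, FS-PT/CPT, leaves open whether hours on the two are added together.

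- If they are added, back-up CPT can keep an FS-PT infant at the AAP level in the analysis.
- An infant between the entry level and the AAP level gets no back-up CPT and can fall under 5 h. A comparable infant in the CPT arm is treated and counted.

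**5. Illustration of bias (assumed rates).** Let true efficacy over all days be 70% for FS-PT, exactly at the margin, and 80% for CPT. A fraction f of FS-PT days is dropped, with efficacy p in those days.

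- Retained FS-PT efficacy: r = (0.70 − f·p)/(1 − f)
- SE = √[0.8·0.2/252 + r(1 − r)/(252(1 − f))]
- Chance of declaring non-inferiority = Φ[(0.10 − (0.80 − r))/SE − 1.96]

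| f | p | r | Shift (points) | False non-inferiority |
|---|---|---|---|---|
| 5% | 60% | 70.5% | 0.5 | 3.4% |
| 10% | 50% | 72.2% | 2.2 | 8.2% |
| 20% | 40% | 77.5% | 7.5 | 49% |
| 5% to 20% | 70% | 70.0% | 0 | 2.5% |

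For the second row, r = (0.70 − 0.05)/0.90 = 0.722, SE = 0.0390, and Φ(0.0222/0.0390 − 1.96) = Φ(−1.39) = 0.082.

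**The case against.** The article never equates bilirubin kinetics with the primary outcome. If the term means a descriptive rate, the endpoint is untouched. That reading is possible, but the primary outcome is itself a bilirubin change per hour of therapy and no other kinetic measure is defined, so the text must at least say which is meant.

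The 65% figure is a treatment target and the 5 hours an analysis condition, so an infant can meet one and fail the other without logical contradiction. This stands. The defect is that infants treated as planned go unanalysed.

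Some rainy-day loss is anticipated in the sample size. That allowance protects numbers. It does not protect against selective loss.

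Several stronger readings are tempting but not supported:

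- **That overheated FS-PT infants are removed by this rule.** Persistent instability and failure to recover within an hour are already excluded by the safe-day rule. Only transient cooling breaks remain. The seven-infant field test in the Background gives an average of 19.7 minutes to return, and a 9:00 to 17:00 day has 8 − 5 = 3 h of slack, about nine such breaks (180/19.7).
- **That CPT infants reach 5 hours routinely.** No CPT hours are given, and the Dehydration section encourages mothers to take CPT infants out for feeding and bathing.
- **That a lost first day is usually the infant's only day.** One day is a planning assumption for a typical course. An infant whose bilirubin remains elevated stays in and can contribute later days.
- **That the preceding observational study sizes the bias.** It reports that "The results showed that FS-PT was efficacious in 94% (164/175) of the infants studied", while 203 infants were enrolled. Counting the other 28 as failures would give 164/203 = 81%. No reason is given for their absence, so they cannot be tied to a 5-hour rule. A single-arm recoding also cannot be set against a between-arm margin. In that study, staying at least 5 hours was part of the definition of success, which is a different use from a condition for being analysed.

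**Conclusion.** The concern holds as a conflict over who enters the primary comparison. Treatment duration applies a 5-hour filter, worded by infant although the endpoint is counted by day. Evaluation criteria and the withdrawal section have no such filter, and it does not fit the planned intent-to-treat analysis. This rests on reading the kinetics as the primary bilirubin change per hour, which is the natural reading.

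Loss through late enrolment affects both arms and costs precision. The risk of bias towards FS-PT comes from FS-PT-only irradiance stops, chiefly in infants between the entry level and the AAP level. The direction depends on dropped days doing worse than retained ones. The size cannot be found from the documents. Under the assumed ranges, false non-inferiority is 3.4% to 49%, with about 8% in the middle case and 2.5% (no inflation) if dropped and retained days perform alike.

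**What to change.** Reconcile Evaluation criteria, the withdrawal section and Treatment duration as follows.

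1. Make the primary intent-to-treat set all safe treatment days with a pre- and post-treatment TSB, analysed by assigned arm whatever hours were achieved.
2. Prespecify the per-hour denominator for short days, for example elapsed time between the two draws. Otherwise a rise of 0.5 mg/dl counts as 0.25 per hour after 2 h of therapy (failure) but 0.07 after 7 h (success). This matters for infants under 72 hours old, where the cut-off is 0.2 mg/dl per hour. For older infants only the direction of change counts.
3. Prespecify a sensitivity analysis for days without a post-treatment TSB, including one that counts them as not efficacious. Making that the automatic primary rule is debatable.
4. Keep days of at least 5 h as a sensitivity or per-protocol analysis, state whether FS-PT and CPT hours are added together, and report hours of therapy by arm.

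The cost is small, because Treatment efficacy already schedules the morning and end-of-day draws and the stated sample size stands. Step 2 is more than wording, since it alters how the endpoint is scaled. Observed efficacy may be somewhat lower, and short days add noise.

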#### Temperature measurements

Infant temperature will be measured hourly while under FS-PT and CPT and monitored based on World Health Organization guidelines for normothermia, hypothermia, and hyperthermia
[30]. For the purpose of this study the normal temperature range of 36.5 to 37.5°C
[30] was modified slightly to 35.5 to 38.0°C in consultation with a neonatologist to provide a broader but safe temperature limit for term and near-term infants. In addition, during the prior safety and efficacy observational study in which infants were monitored closely, no untoward effects of temperatures within the chosen range were reported. If the axillary body temperature falls below 35.5°C the infant will be placed skin-to-skin with the mother and/or brought inside until the temperature returns to the normal range of 35.5 to 38.0°C. If the axillary body temperature goes above 38.0°C, the infant will be brought indoors and/or placed in the shade and/or placed on a wet towel until the body temperature returns to normal at which time FS-PT will resume. The time it takes to return to normal will be recorded. Infants who do not return to normothermia within 1 hour will be taken out of FS-PT for that day. If the axillary body temperature falls below 35°C the infant will be placed skin-to-skin with the mother or wrapped well and brought inside until the temperature returns to normal. If the axillary body temperature goes above 39.0°C, the infant will be brought indoors and placed on a wet towel until the body temperature returns to normal at which time FS-PT will resume. The time it takes to return to normal will be recorded. Infants who do not return to normothermia within 1 hour will be taken out of FS-PT for that day. Infants whose axillary body temperature fall below 35°C or exceed 39°C on two occasions will be excluded from the study.

#### Dehydration

The nurse will also check hourly for clinical signs of dehydration in the form of dry mucus membranes, sunken eyes, dry eyes, and skin tenting. The physician may elect to increase the mother’s breastfeeding frequency while continuing with the FS-PT if the diagnosis is mild dehydration. Whenever the diagnosis of moderate or severe dehydration is made, the infant will be withdrawn from the study for treatment. Because both nutrition and hydration are important in the prevention and treatment of severe NNJ, infants will be allowed and encouraged to breastfeed *ad lib* and often. The FS-PT canopy allows for the mother to stay with the infant and to feed as often as she desires. Mothers will be comfortably seated on custom-made reclined chairs (painted white) and provided with white aprons for breast-feeding or when they need to carry their babies (Figure 
1C). If the mother has chosen to use artificial feeds, those will also be allowed and encouraged *ad lib*. For CPT, the mother will be allowed and encouraged to take the infant out as needed for bathing or feeding.

#### Sunburn

The nurse will assess for sunburn by looking for the onset of pink skin every hour. Most infants are born relatively light skinned and darken over time. Infants born very dark and for whom it would be difficult to recognize pink skin are also much less likely to become sunburned. Absence of sunburn determined in consultation with a dermatologist is defined as the absence of new-onset pink skin. If the infant has the onset of pink skin, the attending physician will be notified and will verify the finding. If the physician makes the diagnosis of sunburn, the infant will be immediately withdrawn from the study. Mothers will be allowed and encouraged as much as possible to stay with their babies, but will be able to leave as needed to care for themselves or other needs. Study nurses will care for the infants during their mother’s absence.

#### Treatment efficacy

Efficacy will be tested by measuring TSB levels prior to the placement of the infant under PT each morning to establish baseline TSB levels. Infants with morning TSB levels that meet the criteria for PT will be randomized for FS-PT. Repeat TSB levels will be obtained at the end of each day spent under FS-PT and between ~4:00 to 5:00 pm for infants under CPT to estimate the effectiveness of the treatment for the day and to determine if the requirement for night-time PT is met.

### Data collection and analysis

Data will be collected on paper case report forms and entered via a web interface into a secure database. The study data will be collected and managed using REDCap (Research Electronic Data Capture) electronic data capture tools hosted at the University of Minnesota’s Academic Health Center. REDCap is a secure, web-based application designed to support data capture for research studies, providing: 1) an intuitive interface for validated data entry; 2) audit trails for tracking data manipulation and export procedures; 3) automated export procedures for seamless data downloads to common statistical packages; and 4) procedures for importing data from external sources.

Demographic data will be summarized and compared between the treatment and control groups using appropriate methods, such as Pearson’s chi-square test for categorical variables and two-sample t-tests for continuous variables. The primary objective is to compare the efficacy of FS-PT and CPT. A 95% exact binomial confidence interval for the true difference in efficacy between the FS-PT treated and CPT control groups will be calculated. FS-PT will be deemed non-inferior to CPT if the calculated confidence interval does not extend more than 10% below the equivalence point.

We plan to conduct three distinct analyses: an intent-to-treat analysis based on the assigned treatment for each enrolled infant, an as-treated analysis based on the actual treatment received on a given day and a per-protocol analysis including only enrolled infants who received the assigned treatment on all of their treatment days.

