### Sample size

The minimum sample size was estimated using the following assumptions: 1) the average efficacy of CPT is 80%; 2) the average efficacy of FS-PT is 80%; 3) there will be the same number of infants assigned to both groups; 4) the delta value is 10% - that is, we want to demonstrate that FS-PT is no more than 10% worse than CPT; and 5) 80% power, one-sided alpha = 0.025.

Under these assumptions, a total of 504 days, or 252 days in each treatment group, will be required. This calculation gives the required number of treatment days that are evaluable for efficacy. Since efficacy will be evaluated only for days in which the treatment was deemed safe, the sample size was increased to account for the possibility that the proportion of safe days might be as low as 90%. Assuming that the safety of both FS-PT and CPT is 90%, a sample size of 560 total days is required. Assuming that a typical course of treatment lasts 1 day, both for FS-PT and CPT, then 560 infants, or 280 infants in each group, will be required. Anticipating up to 10% loss due to rainy days (in the FS-PT group), delisting of infants by parents or guardians, or missing data (in both groups), we will enroll 616 infants, or 308 infants in each group. From our year 1 data in the preceding observational study only 66% of the 826 infants referred for elevated TcB had significant elevated TSB levels, hence 915 infants or more will be enrolled for stage 1 bilirubin estimation until the total requirement of 560 treatment days is reached (Figure 
2).

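### The primary interval treats treatment days as independent although infants are randomised and may contribute several days; the 2.5% one-sided error, and power if recruitment stops on days, are not assured

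*Protocol article*

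**What the plan says.** **Unit of analysis.** Under Evaluation criteria, the average efficacy of each therapy is "defined as the proportion of safe days where a given therapy was used in which the therapy was efficacious". The denominator is days, not infants. The Exit/discontinuation/withdrawal section confirms that every safe day counts.

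**Decision rule.** Data collection and analysis states: "A 95% exact binomial confidence interval for the true difference in efficacy between the FS-PT treated and CPT control groups will be calculated". Non-inferiority is declared if this interval does not reach more than 10 percentage points below equality.

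**Unit of randomisation.** Under Randomization scheme, infants are assigned, one envelope each.

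**Repeated days.** Treatment efficacy has TSB measured every morning before phototherapy and again at the end of the day. An infant completes the protocol only when bilirubin is no longer elevated. The per-protocol set is described as "including only enrolled infants who received the assigned treatment on all of their treatment days".

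**Sample size.** The assumptions are 80% efficacy in both arms, a margin of 10 points, and "80% power, one-sided alpha = 0.025". These give 252 evaluable days per arm, 504 in all, raised to 560 days for 90% safe days. Days become infants by one step: "Assuming that a typical course of treatment lasts 1 day". The section then gives 616 infants as the enrolment target, but also says that stage 1 enrolment continues until 560 treatment days are reached. The abstract gives 616 days.

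**The concern.** A binomial interval for two proportions of days is valid if the days are independent. Days from one infant share that infant's G6PD status, any haemolysis and general course. The protocol itself stresses G6PD deficiency and haemolysis as reasons for high risk. If these traits make a good or bad day more likely to be followed by another of the same kind, the days carry less information than their number suggests and the interval is too narrow. In a non-inferiority trial this error runs in the unsafe direction: FS-PT could be declared non-inferior too easily.

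There are two further consequences. An infant whose bilirubin stays elevated remains in treatment and contributes more days, so the day-level proportion gives more weight to slow responders. And if recruitment stops on a count of days, repeated days reduce the number of infants behind that count.

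The article names the interval and the unit, so this is not a detail left to a later analysis plan.

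**Working it through.** **1. Inputs from the protocol (Sample size).** p = 0.80 in both arms, margin 0.10, one-sided alpha 0.025, power 80%.

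**2. Reproduce the plan's figure.** n per arm = (1.96 + 0.8416)² × 2 × 0.8 × 0.2 / 0.10² = 251.2, so 252 per arm and 504 in total. This matches, as does 504 / 0.90 = 560. Power at 252 per arm is Φ(0.10 / √(0.32/252) − 1.96) = 80.1%. The formula treats all observations as independent.

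**3. Inputs that must be assumed.** The protocol gives no within-infant correlation r; I take 0.3 to 0.5. It gives no distribution of days per infant; I use three scenarios:
- A: mean 1.12 days (about 12% of infants with 2 days). This follows from the preceding observational study, 227 / 203 = 1.12, if its 227 days are treatment days. The wording may instead mean calendar days.
- B: mean 1.5 days (half with 1 day, half with 2).
- C: mean 2 days (40/30/20/10% with 1/2/3/4 days).

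**4. Formulas.** Day counts are unequal, so the design effect is DE = 1 + (m_w − 1) r, where m_w = Σm² / Σm over infants. This gives m_w = 1.21 (A), 1.67 (B) and 2.50 (C).
- One-sided error of the unadjusted interval = 1 − Φ(1.96 / √DE).
- Power of a valid interval with 252 days per arm = Φ(0.10 / √(DE × 0.32 / 252) − 1.96).
- Power with 252 infants per arm: replace 252 by 252 × the mean number of days.
- Days needed per arm = 251.2 × DE, rounded up.

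Example (B, r = 0.3): DE = 1 + 0.667 × 0.3 = 1.20. Error = 1 − Φ(1.96 / 1.095) = 0.037. Power at 252 days = Φ(2.806 / 1.095 − 1.96) = 72.6%.

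**5. Results (r = 0.3 to r = 0.5).**

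| Scenario | DE | One-sided error | Power, 252 days/arm | Days/arm for 80% | Power, 252 infants/arm |
|---|---|---|---|---|---|
| A, mean 1.12 | 1.06–1.11 | 0.029–0.031 | 77.7–76.1% | 268–278 | 82.1–80.6% |
| B, mean 1.5 | 1.20–1.33 | 0.037–0.045 | 72.6–68.1% | 302–335 | 88.1–84.5% |
| C, mean 2 | 1.45–1.75 | 0.052–0.069 | 64.4–56.4% | 365–440 | 90.9–85.1% |

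At r = 0, or with one day per infant, the error is 0.025. Power at 252 days per arm is then 80.1%.

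A beta-binomial simulation with a Wald interval (20,000 runs) gives errors of 0.030–0.031, 0.035–0.043 and 0.052–0.074, in line with the formula.

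**6. What the two recruitment targets imply.** Stopping at 560 treatment days with a mean of 2 days per infant means 560 / 2 = 280 infants. Enrolling 308 infants per arm and losing 10% twice (loss, then unsafe days) leaves 308 × 0.9 × 0.9 = 249 evaluable infants per arm, close to 252. The power statement therefore depends on which target governs.

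**The case against.** The strongest reply is that the protocol expects a typical course of one day, in which case the issue almost vanishes. Scenario A supports this: the error is about 0.03 and the power loss 2 to 4 points. Exact intervals are also conservative, which may offset an effect of that size. This stands, and it limits the size of the point. It does not make the method right, because a typical course of one day is not every course, and the protocol includes all safe days.

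A reader might infer that the 80% power holds only if every infant has exactly one day. The documents do not support that. Power also holds at zero correlation, and in all three scenarios it stays at or above 80% when 252 evaluable infants per arm are reached, because extra days then add information. The Sample size section names 616 infants and at least 915 at stage 1 (915 × 0.66 ≈ 604 reaching treatment). A trial of only 280 infants would sit far below those numbers. The loss of power arises only if the 560-day count is what stops recruitment.

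A reader might also take scenarios B and C as forecasts. Nothing in the protocol supports a mean of 1.5 or 2 days; they show sensitivity only. Nor is positive correlation established: the success criterion changes at 72 hours of age, and infants leave once bilirubin is no longer elevated.

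Finally, the extra weight on slow responders follows from the exit rule, but the documents give neither the size nor the direction of its effect on the comparison. In the as-treated analysis an infant may contribute days to both arms, so the error there may go either way.

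**Conclusion.** The point holds in a limited form. The primary decision rule is a day-level binomial interval, infants are the randomised unit, and the protocol's own procedures foresee repeated days without any rule for them. Under positive within-infant correlation the one-sided error exceeds 2.5%: slightly (about 3%) if infants average 1.12 days, and materially (about 4% to 7%) if they average 1.5 to 2 days. These figures rest on an assumed correlation of 0.3 to 0.5, assumed day-count distributions and a normal approximation.

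The power statement is not wrong in itself: it reproduces exactly for independent days. It is left unassured by two competing recruitment targets, and falls below 80% only if days govern and a valid interval is used. The main harm is the risk of a false non-inferiority claim; the power loss is conditional.

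**What to change.** 1. **Interval.** Replace the day-level binomial interval with one of the following, fixed before the data are analysed:
   - a risk difference with a 95% interval that takes the infant as the cluster, for example GEE with identity link and robust standard errors; or
   - each infant's first safe treatment day as the primary unit, with later days as supportive data. A binomial interval is then valid, the analysis matches the one-day sizing assumption, and the extra weight on infants who stay longer disappears. GEE with working independence corrects the standard error but not that weighting.

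2. **Recruitment target.** Reconcile the 616 infants and 560 treatment days in Sample size, and the 616 days in the abstract, into one target stated in infants. The 616 already given can serve.

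**Cost.** No new data are needed. The first option gives a slightly wider interval if infants have several days; the second drops later days from the primary analysis. The second change fixes a recruitment rule as well as wording, and may lengthen recruitment if the day count would have been reached first. Adjustment for age group or baseline TSB is optional and not needed to correct this error.
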